#### Berlin questionnaire (BQ)

The Berlin questionnaire is a questionnaire used to assess obstructive sleep apnea. It involves 11 items about snoring, breathing problems during sleep and fatigue during wake hours [63]. The BQ has demonstrated validity and sensitivity/specificity [63].

#### World Health Organisation alcohol, smoking, and substance involvement screening test (WHO ASSIST)

Question 2 of the WHO ASSIST requests information on the frequency of use of ten substances during the past 3 months, including substances such as tobacco, alcohol, cannabis, cocaine, amphetamine-type stimulants, inhalants, sedatives, hallucinogens, opioids, and ‘other’ drugs [64]. Responses are scored on a 5-point Likert scale, from ‘never’ to ‘daily or almost daily.’ Reliability of the WHO ASSIST has been demonstrated [65].

#### Return to work questionnaire

Return to work will be measured using a return to work questionnaire designed especially for the study with 5-items related to employment nature and status.

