### Participants

Participants in the RCT will include 120 adults with a chronic SCI living in the community. Inclusion criteria include: (i) aged 18–70 years with SCI living in New South Wales (NSW), Australia; (ii) English speaking; (iii) traumatic/non-traumatic aetiology with complete/incomplete lesions; (iv) at least 12-months post-injury. Exclusion criteria consist of: (i) evidence of severe cognitive impairment as determined by a neurocognitive screen; (ii) evidence of severe respiratory disorder or impaired respiratory function; (iii) evidence of severe psychiatric disorder, such as bipolar disorder or psychoses, determined by psychiatric assessment, and (iv) taking prescribed ß-blockers. Participants for the implementation study will include up to 100 stakeholders and health professional participants. Stakeholders include individuals from relevant government departments and SCI advocacy groups. Health professionals will include those involved in rehabilitation in the hospital and community settings. Participant recruitment for the implementation study will involve convenience sampling through the NSW Agency for Clinical Innovation State SCI Service (SSCIS) Network and personal contacts in relevant health settings.

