### Randomization and blinding

RCT participants will be randomized to either the HRV-F group (*N* = 60) or to the no-treatment control group (N = 60) following a stratified randomization procedure. The randomisation allocation ratio is 1:1, while controlling for covariate level of injury (at and above T3 versus below T3). The randomization sequence will be computer generated via RAND function in Microsoft Excel by an independent person and then be uploaded into REDCap. Once the participant is recruited and completed the baseline assessment, then the assessor will inform the team members who are conducting the intervention. The researcher will then randomize a participant via pre-defined randomization sequence in REDCap (see Fig. 1). Team members responsible for recruitment, assessment and analysing the data will be blinded to group allocation. However, the researcher conducting the intervention as well as the participants will be aware of group allocation given it is not possible to blind them to the HRV-F versus control conditions.

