#### Socio-demographic, injury and medical assessments

Socio-demographic assessment includes sex, age at the time of initial measurement, level of education and employment history. Injury details include age at the time of the SCI, time (years) since the SCI, level and extent (completeness) of the injury using the International Standards for Neurological Classification of SCI (ISNCSCI; https://asia-spinalinjury.org/isncsci-2019-revision). Medical assessment includes medical history (e.g., pre and post-injury health and psychological status), current medications, body mass index assessed from self-reported height and weight, and classified according to World Health Organization guidelines: < 18.5 kg/m^2^ (underweight), 18.5–24.9 kg/m^2^ (normal), 25–29.9 kg/m^2^ (overweight), ≥30 kg/m^2^ (obese).

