### Physiological assessment

See Table 1 for all primary and secondary outcome measures and endpoints (baseline versus 10 weeks, 6 and 12 months) for the RCT and implementation phase. The physiological assessment protocol includes:
(i)Activity #1: 5-min resting baseline (spontaneous breathing) after 2-min habituation;(ii)Activity #2: 5-min Stroop test;(iii)Activity #3: 5-min recovery (spontaneous breathing);(iv)Activity #4: 5-min breathing task (paced breathing at around 6 breath/minute);(v)Activity #5: 5-min recovery (spontaneous breathing).

**Table 1 Tab1:** Schedule of activities and measures for the RCT and implementation study. All psychometric instruments are scientifically validated and reliable

PROJECT STAGE *(number of participants)*			RCT (***N*** = 120) Pilot and main study phase)						Implementation phase (***N*** = 100)
**TIMELINE/PHASES***(D- day, W: week; M: month; Ph: phase)*			**-7D to 0D**	**0D**	**10 W**	**6 M**	**12 M**	**Fortnightly**	**Ph-1 to Ph-5**
**RECRUITMENT**	**ACTIVITIES**	**Mode of data collection**							
Screening	Eligibility checklist	In-person	**✓**						
	ISCoS cardiovascular function dataset	In-person	**✓**						
	ISCoS pulmonary function basic data set	In-person	**✓**						
Consent procedure	Informed consent procedure	In-person	**✓**						
**PARTICIPANT DESCRIPTORS**	**ASSESSMENTS**	**Mode of data collection**							
Socio-demographics	Socio-demographics details	In-person or online		**✓**					
Pre-injury details	Employment history and psychological status	In-person or online		**✓**					
Medical history	Self-report past/present health history	In-person or online		**✓**					
Injury characteristics	Level of lesion, AIS and FIM	Medical records		**✓**					
Pulmonary function	Pulmonary function test	In-person		**✓**					
**ALLOCATION**	**DESCRIPTION**	**Mode**							
Intervention group	HRV-F + Usual care	In-person and online							
Control group	Usual care	Online							
**PRIMARY OUTCOMES**	**OUTCOME MEASURE**	**Mode of data collection**							
Autonomic function	ECG/ HRV Time domain – Short term	In-person		**✓**	**✓**				
	ECG/ HRV Frequency domain – Short term	In-person		**✓**	**✓**				
Cerebral basal artery blood flow	Doppler assessment – Short term	In-person		**✓**	**✓**				
**SECONDARY OUTCOMES**	**OUTCOME MEASURE**	**Mode of data collection**							
Autonomic function	ECG/ HRV Time domain – Long term	In-person		**✓**		**✓**	**✓**		
	ECG/ HRV Frequency domain – Long term	In-person		**✓**		**✓**	**✓**		

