	ADFSCI questionnaire	In-person		**✓**	**✓**	**✓**	**✓**		
Cerebral basal artery blood flow	Doppler assessment – Long term	In-person		**✓**		**✓**	**✓**		
Neurophysiological function	Continuous BP	In-person		**✓**	**✓**	**✓**	**✓**		
	EEG	In-person		**✓**	**✓**	**✓**	**✓**		
	NIRS	In-person		**✓**	**✓**	**✓**	**✓**		
	EOG	In-person		**✓**	**✓**	**✓**	**✓**		
	Skin conductance, BVP, respiration and temp	In-person		**✓**	**✓**	**✓**	**✓**		
Secondary health conditions	SCI-SCS	In-person and online		**✓**	**✓**	**✓**	**✓**		
Cognitive function	NUCOG	In-person and online		**✓**	**✓**				
	Stroop test	In-person and online		**✓**	**✓**				
Psychological/mental health function	GADS	In-person and online		**✓**	**✓**	**✓**	**✓**		
	PHQ-9	In-person and online		**✓**	**✓**	**✓**	**✓**		
Psychosocial function	ISCoS pain questionnaire	In-person and online		**✓**	**✓**	**✓**	**✓**		
	FSS	In-person and online		**✓**	**✓**	**✓**	**✓**		
	PSQA	In-person and online		**✓**	**✓**	**✓**	**✓**		
	PCS	In-person and online		**✓**	**✓**	**✓**	**✓**		
Personal factors	*CD-RISC2 Short Form*	In-person and online		**✓**	**✓**	**✓**	**✓**		
Quality of life	*EQ-5D-5L*	In-person and online		**✓**	**✓**	**✓**	**✓**		
Participation and disability	*WHODAS domain – participation items*	In-person and online		**✓**	**✓**	**✓**	**✓**		
Consumer perception and satisfaction	Self-reported perception of change and satisfaction	In-person and online			**✓**				
Costs for Economic evaluation	Self-reported direct and indirect costs	Diaries (up to 12 m)						**✓**	
Adverse events	*Self-monitoring of Adverse events*	Diaries (up to 12 m)						**✓**	
Self-monitoring *of mood, breath rate, pain, fatigue and sleep quality*	*Numeric rating scale (0 to 10)*	Diaries (up to 12 m)						**✓**	
**EXPLORATORY OUTCOMES**	**OUTCOME MEASURE**	**Mode of data collection**							
Personal factors	*WHO ASSIST*	In-person and online		**✓**	**✓**	**✓**	**✓**		
	*COPE inventory – brief*	In-person and online		**✓**	**✓**	**✓**	**✓**		
	*ADAPSS – Short-form*	In-person and online		**✓**	**✓**	**✓**	**✓**		
	*MSES*	In-person and online		**✓**	**✓**	**✓**	**✓**		
Psychological/mental health function	PTSD Checklist 5	In-person and online		**✓**	**✓**	**✓**	**✓**		
Psychosocial function	SSQ6	In-person and online		**✓**	**✓**	**✓**	**✓**		
	Berlin Questionnaire	In-person and online		**✓**	**✓**	**✓**	**✓**		
Environmental factors	*Care, family and compensation status questionnaire*	In-person and online		**✓**	**✓**	**✓**	**✓**		

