Participation and disability	*RTW Questionnaire*	In-person and online					**✓**		
**IMPLEMENTATION OUTCOME**	**MEASURE**	**Mode of data collection**							
Qualitative/ quantitative assessment	*Stakeholder interviews and surveys*	In-person and online							**✓**

*Abbreviations*: *ADAPSS* Appraisal of DisAbility Primary and Secondary Scale, *AIS* American Spinal Injury Association Impairment Scale, *ADFSCI* Autonomic Dysfunction Following Spinal Cord Injury, *BP* blood pressure, *COPE* Coping Orientation to Problems Experienced, *CD-RISC2* Connor-Davidson Resilience Scale 2 item short form, *ECG* electroencephaolography, *EEG* Electroencephaolography, *EOG* Electrooculography, *EQ-5D-5L* Euro Quality of Life 5-Dimensional 5-level, *FIM* Functional Impairment Scale, *FSS* Fatigue Severity Scale, *GAD-7* Generalized Anxiety Disorder 7-Item Scale, *HRV* heart rate variability, *ISCoS* International Spinal Cord Society, MH, *MSES* Moorong Self-efficacy Scale, *NUCOG* Neuropsychiatry Unit Cognitive Assessment Tool, *NIRS* Near infrared spectroscopy, *PCS* Pain Catastrophizing Scale, *PHQ-9* Patient Health Questionnaire-9, *PSQA* Pittsburgh Sleep Quality Index, *PCL-5* Post-traumatic Stress Disorder Checklist for the Diagnostic and Statistical Manual of Mental Disorders Fifth Version, *RTW* return to work, *SCI* spinal cord injury, *SCI SCS* Spinal Cord Injury Secondary Condition Scale, *SSQ6* Social Support Questionnaire, *Temp* temperature, *WHO ASSIST* World Health Organisation Alcohol, Smoking, and Substance Involvement Screening Test, *WHODAS* World Health Organisation Disability Assessment Scale

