### Statistical methods

Descriptive statistics will be generated for all relevant primary and secondary outcomes at all time-points. Linear mixed models for repeated measures analyses will be used to determine the effectiveness of the HRV-F intervention in autonomic function/HRV and cerebral blood circulation in basal cerebral arteries blood flow. Secondary analyses will determine whether improvements occur in factors such as mental health, cognitive function and sleep associated with the HRV-F intervention. All analyses will be adjusted for factors suspected to confound results, such as education and relevant baseline scores. Latent class mixture modelling will be used to determine trajectories for primary and selected secondary measures like anxiety, depressive mood and quality of life. Missing data will be managed using the linear mixed models, for example, through fitting maximum likelihood estimations generating asymptotically unbiased parameter estimates [68]. Data analyses will be performed using packages such as Statistical Package for the Social Sciences (SPSS version 27, SPSS inc., Chicago, Illinois, USA).

For the implementation study, in which qualitative analyses will also be used, the data will be analysed using valid qualitative packages. Grounded theory, an inductive technique of interpreting the recorded data about the perceptions of the HRV-F and its translation, will be the basis for reaching conclusions about how best to implement and translate the treatment.

For cost-effectiveness, descriptive statistics will be calculated to determine costs and QALYs. The robustness of the costing data will be examined through sensitivity analyses. As in standard economic assessments, costs acquired in this study will likely be skewed, so nonparametric bootstrap methods will potentially be used for testing hypotheses tests and interval estimation. A threshold ICER for Australia will be used to assess value for money.

The ICER will be calculated as per equation (eq. 1) below, that is, the incremental cost per increase in time and frequency domain parameters and as incremental cost per QALY gained in the intervention compared to the controls, in the cost-utility analysis.

1$$ \mathrm{ICER}=\frac{\mathrm{Cost}\ \mathrm{of}\ \mathrm{intervention}\hbox{-} \mathrm{Cost}\ \mathrm{of}\ \mathrm{control}}{\mathrm{Outcome}\ \mathrm{of}\ \mathrm{intervention}\hbox{-} \mathrm{Outcome}\ \mathrm{of}\ \mathrm{control}} $$

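### The exploratory return-to-work questionnaire is scheduled only at 12 months, with no same-form baseline, in people already a year or more past injury

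*Protocol article*

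**What the plan says.** The section on the return to work questionnaire reads: "Return to work will be measured using a return to work questionnaire designed especially for the study with 5-items related to employment nature and status". The five items and their scoring are not shown.

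In Table 1, the row "RTW Questionnaire" stands in the block headed "EXPLORATORY OUTCOMES". Its only tick is in the 12-month column.

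Three other places bear on this:

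- Participants: entry requires people to be "at least 12-months post-injury", aged 18 to 70. No upper limit on time since injury is given.
- Baseline employment data: the socio-demographic assessment includes "level of education and employment history". Table 1 ticks "Employment history and psychological status" at day 0, in a row labelled as pre-injury details.
- Statistical methods: "All analyses will be adjusted for factors suspected to confound results, such as education and relevant baseline scores".

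**The concern.** Return to work is a change of state, but the form that measures it is given once. At a year or more after injury, some participants may have resumed work before enrolment, and others may have retired. A reading of employment status at 12 months alone does not separate those who worked throughout from those who started after allocation.

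What is at stake is precision and interpretation, not bias between the arms. People already working at entry add the same expected share to each arm. That shrinks the visible contrast and adds variance that a baseline covariate could remove. A chance imbalance in employment at entry could also not be recognised. An analysis plan written later cannot supply a baseline reading that was never taken, so this is a matter for the visit schedule.

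**Working it through.** The article gives no figure for return to work, so there is none to reproduce. The check has two parts: what the schedule records, and what a missing baseline could cost under stated assumptions.

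**1. The schedule**

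- Counting columns in the Table 1 row confirms one tick, at 12 months, and none at day 0, 10 weeks or 6 months.
- The other eight exploratory measures (substance use, coping, disability appraisal, self-efficacy, post-traumatic stress, social support, sleep apnoea, and care, family and compensation) are ticked at all four assessments. The last of these is also designed for the study, so an in-house form is no reason to skip baseline.
- The socio-demographic section lists employment history without limiting it to the time before injury. Table 1 puts it in the pre-injury row. Neither place says that work status at enrolment is recorded.
- Baseline assessment precedes randomisation (Randomization and blinding), so day-0 work status would be a proper pre-randomisation covariate.

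**2. Possible loss of precision (assumed rates)**

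Let p0 be the share working at entry, s the share of those still working at 12 months, and r the share of the others who start work. Assume p0 = 0.35, s = 0.90, r = 0.08.

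- Working at 12 months: p1 = p0·s + (1 − p0)·r = 0.315 + 0.052 = 0.367.
- Share of 12-month workers already working at entry: 0.315 / 0.367 = 0.858.
- Correlation of entry and 12-month status: φ = (p0·s − p0·p1) / √[p0(1 − p0)·p1(1 − p1)] = (0.315 − 0.128) / √(0.2275 × 0.2323) = 0.811.
- Variance removable by linear adjustment: φ² = 0.658.
- Unadjusted 95% half-width, 50 per arm (the figure in Power analyses): 1.96 × √(2 × 0.367 × 0.633 / 50) = 0.189.
- Adjusted half-width: 0.189 × √(1 − 0.658) = 0.110.
- Chance standard deviation of the arm difference in employment at entry, 60 per arm: √(2 × 0.35 × 0.65 / 60) = 0.087.

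Over p0 from 0.25 to 0.45, s from 0.80 to 0.95 and r from 0.05 to 0.15, the share already working at entry runs from 0.64 to 0.94, and the removable variance from 0.37 to 0.81.

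**3. Possible dilution (a separate illustration, also assumed)**

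Suppose a share b works at entry in both arms and all of them keep working. Among the rest, 10% start work in one arm and 25% in the other. The arm difference in 12-month work status is then (1 − b) × 0.15. Power is for a two-sided 5% test of two proportions. The last column uses only the 50(1 − b) people per arm not working at entry.

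| b | Difference, points | Power, all 50 per arm | Power, not working at entry |
|---|---|---|---|
| 0 | 15.0 | 0.506 | 0.506 |
| 0.20 | 12.0 | 0.242 | 0.421 |
| 0.35 | 9.75 | 0.162 | 0.353 |
| 0.50 | 7.5 | 0.115 | 0.282 |

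**The case against.** The strongest reply is that employment information is collected at day 0. The socio-demographic section does not restrict it to the time before injury, and a history taken from someone injured a year or more ago may well include current work. A covariate need not come from the same five items. A reader might infer that baseline adjustment is impossible for this outcome. The document does not support that: it leaves open what the history covers. Nor does the adjustment sentence create a contradiction, since it names relevant baseline scores only as an example.

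A reader might also infer that work resumed before randomisation will be scored as a return. That is not established either. The items are not shown, and one of them could ask when work began. Their wording and scoring are details that an article may leave to the full protocol or the form itself.

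Two further replies carry some weight. Another self-report measure, perceived change and satisfaction, is also taken once without a baseline. It asks directly about change and about services received, however, whereas this form is described as covering employment nature and status. And return to work appears in neither the objectives, the power calculation nor the statistical methods, so no main conclusion of the trial depends on it.

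What stands is narrower. No same-form baseline is scheduled, and the document does not say that work status at enrolment is recorded in any other way.

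**Conclusion.** The point holds as a minor one about an exploratory outcome. As scheduled, the return-to-work form yields work status at 12 months, which may not isolate return to work after randomisation. The arm comparison is unbiased, but may be diluted and less precise than it need be.

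The size is not known from the document. In the illustrations, adjustment narrows the half-width from about 19 to 11 points, and restricting to those not working at entry raises power from 0.16 to 0.35 when 35% already work. These figures rest wholly on assumed employment rates, so they do not show that the 12-month result will mainly reflect earlier employment. Even with a baseline, the outcome would remain descriptive at this sample size. If the day-0 employment history does capture current work, most of the loss can be recovered from it.

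**What to change.** Add a day-0 tick in Table 1 for the same five-item questionnaire. For participants already enrolled, use work status at enrolment from the baseline employment history if it was recorded. Analyse 12-month work status in all participants with day-0 status as a covariate, and describe return to work among those not working at day 0.

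The cost is a minute or two of extra questions at an assessment that already takes place, and a small schedule amendment. Participants enrolled before the change will have no same-form baseline.

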#### Environmental factor questionnaire

Care, family and compensation status will be assessed using a questionnaire designed especially for the study with 7-items.

#### Implementation participant survey and semi-structured interviews

Participant surveys will include a mix of positive and negatively phrased closed and open-end questions based on the 14 TDF domains designed to identify facilitators and barriers to the introduction of HRV-F. The semi-structured interviews will ask participants to reflect on the facilitators and barriers identified during the survey and to comment on the practicality and acceptability of potential solutions to identified implementation barriers.

### Economic evaluation

An economic assessment will be conducted that will include costs potentially incurred by participants and healthcare providers. This perspective is required because cost consequences of this study intervention will extend beyond the domain of healthcare. To conduct an economic analysis, the direct and indirect healthcare costs of the intervention and the participants will be acquired from the participant’s cost diaries completed in the study. The economic analyses will include the following:
A cost-effectiveness within-study analysis will be conducted. Incremental cost-effectiveness ratios (ICER) will be calculated for the incremental increase in time and frequency domain parameter in the HRV-F group compared with the Control group.A cost-utility analysis to determine incremental cost per quality-adjusted life-year (QALY) gained. The Australian valuation of the EQ-5D will be used to calculate utility weights on a 0–1 scale where 1 represents very good health and 0 represents death. QALYs will be determined by multiplying utility by duration.

Resources will be valued using standard economic evaluation guidelines. Discounting will be set as 5% into the model.

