#### Resonant frequency

A central goal of HRV-F, therefore, is to establish a participant’s resonant breath rate [14, 19, 37]. Participants utilize feedback of their HRV in exercises to control their autonomic activity using dedicated biofeedback technology and software (ProComp 2 HRV Systems; Thought Technology, Ltd., Canada, www.thoughttechnology.com). In HRV-F, participants initially use this feedback technology to determine their unique resonant breathing rate, which is established over a period of 15 min while reducing their breath rate by 0.5–1 breaths per minute (BPM), and depending on a participant’s initial resting BPM, gradually decreasing BPM down to 4 or 5 BPM over the 15-min. Once participants have identified their unique resonant breathing frequency, they then proceed to perform varied resonant breathing exercises over the 10-week period. The protocol is shown in Fig. 2.

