#### HRV-F training

Ten sessions of formal HRV-F training will be completed over the 10-week intervention. These will involve a mixture of six face-to-face formal sessions (2-h duration each) in the research laboratory and four online/telephone sessions (at-home sessions, up to 1-h duration). Face-to-face HRV-F sessions will be conducted in groups of three participants. However, it is expected that individual sessions will occur given risk of sickness in this population. Self-management strategies will be introduced throughout the 10 weeks of the program, including self-monitoring of mood, anxiety, breath rate, pain/fatigue level and sleep quality, as well as visualisation strategies to be used in conjunction with resonant breathing exercises.

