### Health-related cost, adverse events and monitoring of the mood, breath rate, pain, fatigue and sleep quality

These variables will be measured using a fortnightly participant’s diaries.

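### The economic evaluation takes intervention costs from participants' own diaries, which cannot supply the provider costs that its stated perspective includes

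*Protocol article*

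**What the plan says.** Economic evaluation defines the scope as "costs potentially incurred by participants and healthcare providers", and gives as the reason that cost consequences reach beyond healthcare. It then names one data source: "direct and indirect healthcare costs of the intervention and the participants will be acquired from the participant’s cost diaries completed in the study". Intervention costs are thus expressly included among what the diaries are to supply.

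Two other places describe the diary. Table 1 lists the cost measure as "Self-reported direct and indirect costs", collected fortnightly in diaries for up to 12 months. The section on health-related cost, adverse events and monitoring says "These variables will be measured using a fortnightly participant’s diaries".

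The resources used in delivery are described elsewhere. HRV-F training sets out "six face-to-face formal sessions (2-h duration each) in the research laboratory and four online/telephone sessions", the latter lasting up to 1 h each, and adds: "Face-to-face HRV-F sessions will be conducted in groups of three participants". Individual sessions are also expected. Resonant frequency says that participants use "dedicated biofeedback technology and software". Home practice adds weekly telephone support. Under Control group protocol, controls receive reading material and a brief weekly call.

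Eq. 1 in Statistical methods divides the difference in cost between arms by the difference in outcome. It is used for the HRV parameters and for QALYs.

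**The concern.** The stated source does not match the stated perspective. Participants can report travel, lost time, out-of-pocket spending and their use of services. Nothing in the article has them paying for, or recording, the therapist's hours, the laboratory, or the biofeedback equipment and software. These are provider costs, and they make up the core cost of delivering HRV-F.

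If only diary costs enter Eq. 1, most of the delivery cost is absent from the intervention term, while the control arm loses far less. Incremental cost is then too low, and wherever the outcome difference favours HRV-F the ICER is too low as well. Both planned ICERs share this numerator. The cost-utility result is to be judged against an Australian threshold, so an understated numerator could change the value-for-money conclusion.

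**Working it through.** The article gives no cost, QALY or ICER figure, so there is nothing to reproduce. The check has two parts.

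**1. What is required against what is collected**

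| Item | Within the perspective? | Can a participant's diary supply it? |
|---|---|---|
| Participants' own spending, time and service use | Yes | Yes |
| Staff time for face-to-face and remote sessions | Yes (provider) | No |
| Biofeedback hardware and software | Yes (provider) | No |
| Weekly calls, both arms | Yes (provider) | No |
| Reading material, controls | Yes (provider) | No |

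**2. Size of the staff-time gap**

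Inputs from HRV-F training: 6 face-to-face sessions of 2 h, groups of 3 or individual, and 4 remote sessions of up to 1 h. There are 60 HRV-F participants.

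Assumptions: one staff member per session, full attendance, remote sessions individual and at their 1-h maximum, and AU$50-120 per staff hour. The article gives no rate.

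Staff hours per participant = (6 × 2) / group size + 4 × 1

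- Groups of three: 12/3 + 4 = 8 h
- Individual: 12 + 4 = 16 h

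Over 60 participants: 8 × 60 = 480 h and 16 × 60 = 960 h.

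Omitted cost per participant = hours × rate

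- Groups of three: 8 × 50 = AU$400 to 8 × 120 = AU$960
- Individual: 16 × 50 = AU$800 to 16 × 120 = AU$1,920

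Equipment, software and calls are not in these figures.

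**Effect on the cost-utility ICER, for illustration.** Shift = omitted cost / QALY gain. At an assumed gain of 0.02 QALY the shift is 400/0.02 = AU$20,000 to 1,920/0.02 = AU$96,000 per QALY. Over assumed gains of 0.05 down to 0.01 it runs from 400/0.05 = AU$8,000 to 1,920/0.01 = AU$192,000. The direction does not depend on these choices as long as the gain is positive. The size does.

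**The case against.** The best defence is that the intention to count provider costs is explicit. The section opens with them, says resources will be valued by standard guidelines, and plans sensitivity analyses of the costing data. A staff-time log is the sort of detail a condensed article leaves to the full protocol, and planned delivery can be costed from the session schedule without new data. The economic evaluation is also not among the listed primary or secondary objectives.

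Part of this stands. The intention is clear, planned delivery can indeed be costed from the schedule, and the effectiveness conclusions are unaffected. But this is not a case of missing detail: the article states a source, applies it to intervention costs, and that source cannot deliver them. Valuation guidelines set unit prices and do not say where quantities are recorded. Sensitivity analyses and the bootstrap work on the costs collected, so a cost never entered is absent from every replicate.

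The objection that the hours are not a floor is also right. Remote sessions may be shorter than 1 h and attendance may be incomplete, so 8 h and 16 h are read here as upper values for each format.

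Three stronger readings are tempting and are not supported:

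- A reader might infer that the omission falls on the HRV-F arm alone. Controls receive weekly calls and reading material, which the diaries would also miss. The call element partly cancels in the increment; the treatment sessions and biofeedback equipment do not.
- A reader might infer from Eq. 1, or from "descriptive statistics will be calculated to determine costs and QALYs", that QALYs enter as raw arm differences and bias the ICER. Eq. 1 is the generic definition and does not say raw or adjusted. Statistical methods also states that all analyses will be adjusted, including for relevant baseline scores. Even an unadjusted difference is unbiased under randomisation, and only less precise.
- A reader might infer that the diary source makes the ICER unstable. It shifts the numerator in a known direction. Sampling uncertainty is a separate matter, which the planned bootstrap and acceptability curves address.

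**Conclusion.** The point holds for the cost side. As written, the Economic evaluation section gives intervention costs a source that cannot meet its own perspective, so incremental cost is understated, mostly through the HRV-F arm, and the ICER is biased in favour of HRV-F.

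The omitted staff time is up to about 8 h per participant in groups of three and up to 16 h if individual. That is about AU$400-1,920 per participant before equipment. The session numbers, lengths and group size are the protocol's. The hourly rate, one staff member per session and full attendance are assumptions, and the ICER shifts also rest on assumed QALY gains. All of this presumes that the stated source is followed and no other is used.

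This should be corrected, but it is confined to the economic evaluation. No fault is found with the planned handling of QALYs.

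**What to change.** Amend the Economic evaluation section so that delivery costs in both arms come from trial or provider records: session attendance, actual group size, staff hours, a share of equipment and software, weekly calls, and reading material. Exclude research-only assessments and gift cards. State that the diaries cover participants' own costs and their health-service use.

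Optionally, add a sentence confirming that the baseline adjustment in Statistical methods also applies to QALYs, using baseline EQ-5D utility. This is a clarification and does not correct an error.

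The cost is slight extra record-keeping, best begun while sessions are being delivered, and probably a less favourable ICER.
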